#### Sample size

2.5.1.

The CARRDIP randomized trial was designed to detect a clinically relevant difference in maternal cholesterol levels at week 36 in pregnancy and in neonatal cholesterol levels (26). In the CARRDIP20 study, we examined differences in CVD risk factors, which are typically in the range of 0.5–0.7 standard deviations (SDs) in intervention trials with groups randomized to different diets (45), requiring a sample size of approximately 64–100 per group with 80% power at a 5% significance level. Thus, despite the expected loss to follow-up, we most likely have statistical power to detect clinically relevant differences between the groups (46). If we assume an average difference in the systolic blood pressure of 5 mmHg, with SD = 10 mmHg, we will need 128 participants (64 in each group; power 80%, significance level 5%). This corresponds to 47% of the mothers that participated in the CARRDIP trial.

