#### Data analysis

2.5.2.

The differences between the intervention and control group in primary and secondary outcomes will be analyzed separately for the mothers and offspring. We will follow the CONSORT guidelines (47–49). The primary outcome, blood pressure, and the majority of the secondary outcomes are continuous with two time points: baseline and a 20-year follow-up. Analysis of covariance will be used to analyze the data (50). There may be some selection of participants in a long-term follow-up. We can adjust for variables that differ between the intervention and control group and are associated with the outcome of interest (48). However, the use of analysis of covariance (i.e., adjustment for the baseline value) may have to be evaluated if there are major indications of selective drop-out. In that case, we will analyze the difference between the values observed at the 20-year follow-up and the baseline using a multivariable linear regression model and adjust for potential covariates.

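### An undefined drop-out trigger swaps baseline adjustment for a change score, which cannot be formed for offspring blood pressure and costs power for maternal outcomes

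*Protocol article*

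**What the plan says.** Section 2.5.2 (Data analysis) describes the data this way: "The primary outcome, blood pressure, and the majority of the secondary outcomes are continuous with two time points: baseline and a 20-year follow-up". The default follows: "Analysis of covariance will be used to analyze the data". The section allows that attendance after 20 years may be selective and continues that "the use of analysis of covariance (i.e., adjustment for the baseline value) may have to be evaluated if there are major indications of selective drop-out". The consequence is then stated: "In that case, we will analyze the difference between the values observed at the 20-year follow-up and the baseline". The model is a multivariable linear regression with covariates that are not named.

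Section 2.5.1 (Sample size) sets the scale: "If we assume an average difference in the systolic blood pressure of 5 mmHg, with SD = 10 mmHg", and from this "we will need 128 participants (64 in each group; power 80%, significance level 5"%). It adds: "This corresponds to 47% of the mothers that participated in the CARRDIP trial". Section 2.5 (Outcomes) names offspring blood pressure as primary and mentions offspring readings at 1 and 3 years. Section 2.2 (Design and setting) also refers to systolic pressure at 6 months.

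**The concern.** The rule lets the attendance data decide the estimator, without saying what pattern would trigger the change or why a change score would be the better tool. If the planned 128 attend, more than half the cohort is missing, so some sign of selection is likely and the rule may well be invoked.

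Two things are at stake. The primary analysis could move to a quantity that does not exist for the offspring. For the mothers, it could move to a less precise estimator whose benefit against selection depends on assumptions that the article does not state.

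**Working it through.** **The plan's own figure.** A two-sided t-test at 5% and 80% power with difference 5 and SD 10 (0.5 SD) needs 63.8, so 64 per group and 128 in all, as stated. 128/269 = 47.6%, in line with the stated 47%. This calculation compares follow-up values only and uses no baseline correlation.

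**Primary outcome.** Women entered at gestational weeks 17–20 (section 2.3), so no blood pressure of the child before randomisation is possible. The earlier offspring readings that the article mentions (6 months, 1 year, 3 years) all follow the intervention. If the diet shifted blood pressure by an amount e₁ in childhood and e₂₀ at 20 years, the change score estimates e₂₀ − e₁, not e₂₀. Any effect already present in childhood is subtracted.

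**Maternal outcomes with a baseline: precision.** Assume the same SD σ at both times and correlation r.
- Change score: residual variance 2σ²(1 − r).
- Analysis of covariance: residual variance σ²(1 − r²).
- Difference: σ²[2(1 − r) − (1 − r²)] = σ²(1 − r)², which is positive for every r < 1.

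The effective standardised difference is 0.5/√(2(1 − r)) for change and 0.5/√(1 − r²) for analysis of covariance. With 64 per group (two-sided t-test):

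| r (assumed) | Power, change | Power, ANCOVA | n per group for 80%, change |
|---|---|---|---|
| 0.1 | 55% | 81% | 114 |
| 0.2 | 60% | 82% | 102 |
| 0.3 | 66% | 84% | 89 |
| 0.4 | 73% | 86% | 77 |
| 0.5 | 80% | 90% | 64 |
| 0.7 | 95% | 98% | 39 |

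Below r = 0.5 the change score is worse than ignoring baseline altogether (80%).

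**Maternal outcomes with a baseline: bias.** Let D be the baseline difference between the attending arms. If attendance depends on baseline differently by arm, the expected follow-up difference with no true effect is rD. The change score gives rD − D = −(1 − r)D, while analysis of covariance removes rD and leaves 0. With r = 0.2 and D = 3 mmHg, the bias is −0.8 × 3 = −2.4 mmHg, about half the planning difference.

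That is only one mechanism. Large simulations (2,000,000 subjects, no true effect, SD 10, selection in one arm only) give these biases in mmHg:

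| Attendance depends on | Estimator | r = 0.2 | r = 0.3 | r = 0.5 | r = 0.7 |
|---|---|---|---|---|---|
| Baseline | Change | +3.3 | +2.9 | +2.1 | +1.3 |
| | ANCOVA | 0.0 | 0.0 | 0.0 | 0.0 |
| Stable latent trait | Change | 0.0 | 0.0 | 0.0 | 0.0 |
| | ANCOVA | −1.5 | −1.6 | −1.5 | −1.1 |
| 20-year value | Change | −3.3 | −2.9 | −2.1 | −1.2 |
| | ANCOVA | −4.0 | −3.8 | −3.2 | −2.2 |

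The first row agrees with the formula: D was about −4.1, and at r = 0.2, −0.8 × (−4.1) = +3.3.

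**False-positive rate.** For trials of 269 with about 48% attending, r = 0.2, and attendance log-odds of +0.3 per SD in one arm and −0.3 in the other:
- Baseline-driven: change about 19–20%, ANCOVA about 5%.
- Latent trait: change about 5%, ANCOVA about 10%.
- Driven by the 20-year value: change about 20%, ANCOVA about 40%.

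Opposite directions in the two arms is an extreme pattern. With a slope of +0.3 in both arms, both methods have bias near 0 and about 5% false positives under all three mechanisms.

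**The case against.** The strongest objection is that distrust of baseline adjustment under selective attendance has a sound basis. If people stay away because of a stable trait that affects both measurements equally, the change score cancels it and analysis of covariance does not. This stands. A reader might infer that the change score is always the more biased choice when drop-out is selective. The article names no mechanism, and two of the three examined here point the other way.

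A reader might also infer that the estimator could be chosen to suit the result. That is not shown. Attendance can be judged from baseline data before outcomes are compared, and section 2.4 says the investigators are blinded to allocation. What is shown is dependence on the attendance data.

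The trigger and the covariate list may be set out in an analysis plan that is not shown, so their absence alone is no fault. The switch itself, however, is stated. If baseline were among the unnamed covariates, the treatment estimate would equal that from analysis of covariance and the switch would do nothing. The natural reading is that baseline adjustment is dropped.

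Two further limits are fair. The missing offspring baseline affects the default as much as the fallback, so it does not favour one over the other. And maternal blood pressure is not in the article's list of secondary outcomes, so the mmHg figures illustrate scale. The power figures, in SD units, carry over to any continuous maternal outcome with a pre-randomisation value. At r of 0.5 or more, the change score still reaches the planned 80%.

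**Conclusion.** The concern holds in limited form. The switch cannot be carried out for the primary outcome as described. For maternal outcomes with a baseline, it makes a less efficient estimator depend on an undefined reading of attendance, "may have to be evaluated if there are major indications of selective drop-out", with no dependable gain against bias. At 64 per group and 0.5 SD the power cost is about 10 points at r = 0.5 and over 20 points at r = 0.2, but only about 2 points at r = 0.7.

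These figures assume equal SDs at both times and a range for r, which the article does not give. The −(1 − r)D bias and the 19–20% false-positive rate belong to one mechanism, attendance that depends on baseline differently by arm, and must not be read as the general effect of the fallback. This should be corrected before analysis. It is cheap to fix and does not undermine the study.

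**What to change.** Delete the conditional move to change scores and fix one primary analysis whatever the attendance pattern:
- **Mothers:** baseline-adjusted regression for outcomes that have a pre-randomisation value.
- **Offspring:** regression of the 20-year value on allocation and named pre-randomisation maternal covariates, for example age and body mass index. Do not describe this as adjustment for, or change from, an offspring baseline.
- **Selective attendance:** compare the original baseline data of attenders and non-attenders by arm. Then report a prespecified inverse-probability-weighted or multiply imputed analysis, plus one sensitivity analysis that allows attendance to depend on unobserved values. A change-score analysis may stay here for the mothers, with its assumption of a stable trait stated.

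The cost is a few sentences in section 2.5.2 and a little more analysis work. No new data are needed, and no power is lost in the primary analysis.

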## Discussion

3.

The existing evidence suggests that maternal diet during pregnancy may impact the health status of the offspring. Moreover, observational studies support the significance of the *in utero* metabolic environment on the risk of CVD in the offspring later in life (51, 52). The data from the randomized controlled CARRDIP trial with significant clinical effects in both mother and offspring offer a unique possibility to study possible mechanisms for the observed differences. Furthermore, it is crucial to identify possible targets for appropriate dietary intervention during pregnancy to optimize the health of the offspring, both *in utero* and later in life. Ideally, these potential targets should be investigated through long-term follow-ups of RCTs.

To date, studies investigating the effects and mechanisms of diet on the long-term health of the child have primarily been observational and animal studies. Thus, the proposed CARRDIP20 study of the long-term (20 years) effects of a Mediterranean diet during pregnancy on offspring health is unique and of potential great clinical and scientific interest.

Pregnancy may be regarded as a “window of opportunity” where interventions can promote the long-term health outcomes of both the mother and the offspring. Further identification of mechanisms responsible for fetal programming of adult CVD may identify possibilities for targeted treatment among groups at risk of CVD, as well as improved dietary recommendations and policy strategies to improve health in the general population.

## Data Availability

The datasets generated and analyzed during the current study will not be publicly available due to privacy concerns of participants in the study. Restrictions apply to the availability of these data, which were used under license for the current study, but are available from the corresponding author on reasonable request and with permission from Committees for Medical and Health Research Ethics, Norway.
